# Do antibacterial skin sutures reduce surgical site infections after elective open abdominal surgery? - Study protocol of a prospective, randomized controlled single center trial

**DOI:** 10.1186/s13063-019-3492-3

**Published:** 2019-07-02

**Keywords:** Surgical site infection, Antibacterial-coated suture material, Triclosan, Elective abdominal surgery, Skin closure

## Abstract

**Background:**

Surgical site infections (SSI) remain one of the most common complications in conventional abdominal surgery with an incidence between 4% and 19% (Sandini et al., Medicine (Baltimore) 95:e4057, 2016) in the literature. It is unclear whether the use of coated suture material for skin closure reduces the risk of SSI. In line with in-vitro results, we hypothesize that the use of antibacterial skin sutures (triclosan-coated poliglecaprone 25) reduces the rate of SSI after open abdominal surgery.

**Methods/design:**

To prevent SSI, triclosan-coated poliglecaprone 25 sutures will be tested against un-coated suture material for skin closure after elective open abdominal surgery of 364 patients. The study is planned as a single-center, prospective randomized controlled trial. Patients will be followed for 30 days after surgery to detect and document wound complications. The rate of SSI after 30 days will be analyzed in both groups.

**Discussion:**

If we can confirm the proposed hypothesis in our study, this could be a promising and feasible approach to lower SSI after open abdominal surgery. By lowering the rate of SSI this might offer a cost-saving and morbidity-reducing procedure.

**Trial registration:**

German Clinical Trials Register, DRKS00010047. Registered on 05.01.2017.

**Electronic supplementary material:**

The online version of this article (10.1186/s13063-019-3492-3) contains supplementary material, which is available to authorized users.

## Background

Surgical site infections (SSI) are a risk inherent to surgical procedures and a frequent complication, notably after digestive surgery. SSI are associated with severe morbidity and mortality, especially in high-risk patient populations [1, 2]. According to Center for Disease Control (CDC) guidelines [1], SSI up to 30 days after surgery are included, or even a year later when a foreign material such as a prosthesis has been implanted. SSI can be classified as superficial if they involve the skin only or subcutaneous tissue at the site of the incision, deep when they affect more internal structures of the abdominal layer, and organ-spaced when they also involve the abdominal cavity and the space between the organs that were manipulated or opened during the surgical procedure [3, 4]. The cornerstones for reducing the risk of SSI include exquisite surgical technique, timely and appropriate antimicrobial prophylaxis [5], effective and persistent skin antisepsis, and identification of adjunctive strategies for reducing wound contamination [6] and promoting wound healing. SSI are primarily caused by Gram-positive organisms from the patient’s own flora on the skin, mucous membranes, or hollow viscera manipulated during surgical procedures [1].

Various bacteria may contaminate not only the tissue in a surgical wound but also the actual suture material. If the surgical suture is implicated as the cause of a wound infection, then an antibacterial coating should nearly eliminate the possibility of the suture material becoming a vector of infection. The use of antibacterial-coated medical devices has become widespread. Numerous biomedical devices, including urologic and central venous catheters and orthopedic, vascular, and cardiothoracic implants, are commercially available with antibacterial impregnation or surface coatings.

It has been reported that percutaneous sutures approximating skin edges were often colonized from the body surface into the wound track by strains of *Staphylococcus epidermidis* capable of producing an amorphous extracellular matrix (biofilm), protecting the microbial populations from host defense factors [7]. Triclosan as a broad spectrum antiseptic is known from in vitro and in vivo studies to reduce the adherence of selective clinical Gram-positive, Gram-negative, drug-resistant, and biofilm-forming strains to the surface of a widely used braided surgical suture (polyglactin 910). Triclosan-coated polyglactin 910 sutures exhibit an antibacterial activity sufficient to prevent in vivo bacterial colonization in a guinea pig model [8]. Further, it is documented to be safe and efficient [2] and did not adversely affect wound healing in patients undergoing general surgical procedures [9]. In view of the high frequency of SSI and its substantial impact on morbidity and mortality, the reduction of the SSI rate should be a major priority among all surgical disciplines.

Therefore, our objective is to determine whether subcuticular closure of an abdominal wound with triclosan-coated Monocryl plus® running skin sutures influences the rate of SSI at 30 days following elective abdominal surgery when compared to similar uncoated Monocryl® sutures. Secondary objectives are to determine whether the use of triclosan-coated sutures reduce the length of hospital stay, wound dehiscence, and mortality rate at 30 days and number of re-operations in the same 30-day period following surgery.

In line with in vitro results, we hypothesize that the use of antibacterial skin sutures (with triclosan-coated poliglecaprone 25) reduces the rate of SSI after open elective abdominal surgery. The postulated mechanism states a reduced colonization of poliglecaprone 25 sutures by several strains of bacteria when antibacterial-coated suture material is used.

The study protocol has been written in accordance with the Standard Protocol Items: Recommendations for Interventional Trials (SPIRIT) checklist (Additional file 1).

## Methods/design

This single-center prospective randomized controlled trial (RCT) is conducted at the Department of General-, Visceral- and Thoracic Surgery and the Department of Obstetrics and Gynecology at the AGAPLESION Diakonie Hospital Rotenburg (Wuemme) gGmbH, Germany. It is designed as a double-blind parallel-group superiority trial.

All patients planned for elective open general/colorectal or gynecological abdominal surgery will be consecutively informed about the study. Informed consent will be signed by each participating patient and a member of the study team at least 24 h before elective surgery. A flow diagram for this trial is shown in Fig. 1.

**Fig. 1 Fig1:**
[figure not shown]
Schedule of assessments and procedures. Crosses indicate assessments for all registered patients and circles assessments of all randomized patients. ^1^Assessments for all registered patients with implanted foreign body during surgery

Baseline data such as gender, age, body mass index (BMI; calculated by Weight/Height^2^) will be collected from all included patients. Furthermore, factors that might influence the outcome of the surgery will be recorded. These factors include, but are not limited to, American Society of Anesthesiologists (ASA) classification, diabetes mellitus, antidiabetic medication, present immunosuppression, wound class according to CDC criteria (clean/clean-contaminated/contaminated/dirty), type of incision (transverse/longitudinal), operative time, amount of blood loss, length and orientation of incision.

### Randomization and intervention

After written informed consent is obtained, patients eligible for the study, will be randomized intraoperatively into two groups:Group A: Skin closure with non-coated suture material poliglecaprone 25 (Monocryl®, Ethicon GmbH, Norderstedt, Germany)Group B: Skin closure with triclosan-coated poliglecaprone 25 (Monocryl® Plus Ethicon GmbH, Norderstedt, Germany)

The randomization sequence is performed with sealed opaque envelopes. The patients are block randomized with equal block sizes of 20 items per block (allocation of patients per block is 1:1). The randomization list generation is computer-based using the *Random Allocations Software Version 1.0.0* (Freeware) by M. Saghaei, MD.

#### Surgical procedure

A perioperative antibiotic prophylaxis (standard dose) is administered to each patient 30–60 min prior to surgery (first or second class cephalosporin). Wound opening by the surgeon is performed in layers with:Skin incision with scalpelPreparation of the subcutaneous tissue with monopolar cautery, scalpel, or scissorsIncision of the muscle fascia with diathermy, scalpel, or scissors

Wound closure is performed in layers with:Running sutures for the rectus fascia with Everett suture (Maxon® 1, Covidien IIc, Mansfield, USA)No subcutaneous sutures are added

A scrub nurse who is not involved in the patients’ follow-up will open the randomization envelope in the operation room and deliver the suture material to the scrub nurse immediately before wound closure. The scrub nurse hands over the sutures to the surgeon without showing the package of suture material. Macroscopically it is impossible to distinguish between Monocryl® and Monocryl® plus sutures. Consequently, the surgeon as well as the patients are unaware of the assigned treatment group.

Finally, intracutaneous skin closure with running stitches (using either Monocryl® or Monocryl® Plus) is performed by the surgeon and sterile wound dressing (Curapor, Lohmann & Rauscher, Germany) is applied.

In none of the cases will a wound drainage (superficial or deep) be set in place. According to the CDC guidelines [1], a follow-up of 30 days is required.

The operating surgeon, his team, and ward residents as well as the patients are unaware of assigned treatment groups. The operating surgeons and their teams will perform routine wound surveillance according to clinical standards, including diagnosis and treatment of SSI. Wound photographs will be taken on days 3 and 7 by the resident in charge, who is blinded as well.

The resident in charge on the ward is responsible for registration of SSI. If a SSI is detected by the resident, it needs to be verified by the consultant surgeon in charge. In addition, inpatients are seen regularly by members of the study team. Thus, appropriate sensitivity to detect in-hospital events can be provided. For post-discharge follow-up at day 30, well-trained investigators blinded to treatment allocation will examine any patient in an outpatient setting and document wound status by photograph. When SSI is present, clinically relevant microbiological samples are cultured as needed, and the patient receives standard wound therapy. In case of an implanted foreign body during surgery, an additional assessment including wound photography is performed in an outpatient setting one year after surgery.

To ensure appropriate specificity, all cases of SSI are validated by a board-certified wound care specialist who is blinded to the intervention.

### Outcome measures

#### Primary outcome measure

Occurrence of any SSI within 30 days after surgery (within one year after implantation of foreign body)

In the present study, all types of SSI are considered for the primary outcome. SSI are defined as incisional (either superficial or deep) infection or organ-space infection according to CDC criteria [1]. Superficial incisional SSI include skin and subcutaneous tissues, deep incisional infections involve fascia and muscle, and organ-spaced infections involve any organ or space other than the incised layer of body wall that was opened or manipulated during surgery.

#### Secondary outcome measures

Wound dehiscence and re-operation rate due to wound dehiscence within 30 days, all-cause 30-day mortality, and length of hospital stayOccurrence of any SSI within one year after implantation of a foreign body

Furthermore, we will evaluate potential risk factors for poor wound healing, such as gender, age, BMI, ASA classification, diabetes mellitus, antidiabetic medication, present immunosuppression, wound class according to CDC criteria, operative time, amount of blood loss, length, and orientation of incision [3, 10].

### Ethical considerations

The study was approved by the local ethics committee (Ethics Committee of the Georg-August University of Goettingen, Germany; 8/7/12). The study was registered at germanctr.de, ID DRKS00010047.

Informed consent, patients’ information, follow-up sheets, as well as the study protocol have been submitted.

All eligible patients will be precisely informed about the study and study-related procedures by a member of the study team. Patients declining participation in the trial will be excluded as the trial is strongly voluntary.

Both skin suture materials (Monocryl®, Monocryl® Plus) are officially available on the market in Germany and tested concerning safety [2]. Both are CE certified.

### Inclusion criteria

All patients from the Department of General-, Viceral- and Thoracic Surgery of AGAPLESION Diakonie Hospital Rotenburg (Wuemme), Germany and the Department of Gynecology and Obstetrics of the AGAPLESION Diakonie Hospital Rotenburg (Wuemme), Germany planned for open elective abdominal surgery ≥ 18 years old will be screened for inclusion.

Open abdominal surgery is defined as surgically opened peritoneal cavity.

### Exclusion criteria

Participation in a clinical study in the last 3 monthsFactors limiting the ability to co-operate in the studyAbsence of signed informed consent before entering the studyAny drug, alcohol, or nicotine abusePeople with mental disordersPregnant womenParticipants under 18 yearsEmergency surgery/procedures

### Statistics/sample size calculation

The sample size is estimated on the basis of a two-sided chi^2^ test for equality of the proportions of SSI occurrence within 30 days in the treatment and control groups (null hypothesis). Based on evidence in the literature, an infection rate of 12% is assumed for the control group and it is expected that the use of antibacterial sutures will reduce the SSI rate to 4% in the treatment group [11, 12].

Thus, a treatment effect of − 0.08 is assumed (i.e., an absolute risk reduction of 8 percentage points). Furthermore, the significance level of the test is set to 5% and a power of 80% is desired. To determine the sample size, we generate 10,000 synthetic data sets for a range of potential sample sizes using the above-mentioned assumptions for the SSI rates in both study groups. That is, we generate realizations of independent binomial random variables with probabilities of SSI occurrence p_T_ = 0.04 and p_C_ = 0.12, respectively. With each bi-variate data set, the two-sided chi^2^ test is performed at level α = 0.05.

Then, the power associated with a particular sample size n results in the H_0_-rejection rate across the 10,000 tests performed with data sets of size n. Hence, we obtain the power of the test as a function of the sample size and can identify the best value of n corresponding to a power of at least 80%. All computations are performed in the statistical software environment R (R Core Team, 2018, *R: A Language and Environment for Statistical Computing*. R Foundation for Statistical Computing, Vienna, Austria).

We find that, given a test level of α = 0.05, a total of 344 patients are needed to show that the SSI rates are different with a power of at least 80%. Furthermore, accounting for an expected drop-out rate of 5%, we obtain the number of *N* = 364 study participants to be recruited, that is, 182 patients for each study group.

All analyses will be performed after termination of the main part of the trial, that is, after the last 30-day follow-up visit has taken place.

The full analysis set (FAS) will include all study participants who were randomized and for whom data from at least one follow-up visit are available.

The per protocol set (PPS) will include all study participants in the FAS for whom the intervention was completed as planned and for whom complete data on all endpoints

are available.

All statistical analyses will be performed on the FAS according to the intention-to-treat principle. In addition, all analyses will be repeated using the PPS instead to assess the robustness of the findings.

The primary analysis investigates whether the SSI rate (within 30 days) among patients receiving antibacterial sutures is different from the rate in the control group, using a two-sided chi^2^ test for equality of proportions (null hypothesis) at significance level α = 0.05.

Besides the test result, the estimated SSI rates in the two groups and the estimated SSI rate difference will be reported with their 95% confidence intervals, the latter describing the precision of the estimates.

In addition to the primary analysis, we will assess the difference between the treatment and control groups when controlling for general risk factors for poor wound healing such as age and BMI of a patient or length and orientation of the incision. This will be achieved by evaluating the odds ratio obtained from estimating a multiple logistic regression model for the binary endpoint SSI (within 30 days) with explanatory factor treatment and adjusted for risk factors for poor wound healing. To further explore potential benefits of using antibacterial sutures, the differences between the treatment and control groups regarding the following secondary endpoints will be assessed:Wound dehiscence within 30 days (yes/no)Re-operation due to wound dehiscence within 30 days (yes/no)Death within 30 days (yes/no)Length of hospital stay (days)

The first three secondary outcomes will be analyzed estimating simple and multiple logistic regression models with explanatory factor treatment and, in the multiple case, adjusted for general risk factors for poor wound healing. The secondary endpoint length of hospital stay will be assessed using Poisson regression models instead.

For the subgroup of patients whose surgery involves the implantation of a foreign body, an additional long-term follow-up visit will take place one year after surgery. Once these data are collected, a final secondary analysis will be done for this subgroup of patients evaluating their SSI risk (within one year).

For all secondary analyses, parameter estimates and odds ratios will be reported together with 95% confidence intervals. If *p* values are reported, they will be interpreted as continuous measures of evidence against the associated null hypotheses.

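### The full analysis set requires a post-randomisation visit, so it is not intention-to-treat and drops early deaths from the 30-day mortality endpoint

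*Protocol article*

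**What the plan says.** All of this is in the protocol article.

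- **FAS.** Statistics/sample size calculation admits patients "who were randomized and for whom data from at least one follow-up visit are available".
- **Principle.** The same section says: "All statistical analyses will be performed on the FAS according to the intention-to-treat principle".
- **Mortality.** Secondary outcome measures lists "all-cause 30-day mortality". The statistics section repeats it as a yes/no endpoint for logistic regression and names no separate analysis set. Length of stay is also analysed on the FAS.
- **Per-protocol set (PPS).** FAS members "for whom the intervention was completed as planned and for whom complete data on all endpoints" are available. Repeating the analyses on this set is the stated robustness check.
- **Timing.** Patients "will be randomized intraoperatively into two groups" (Randomization and intervention).
- **Contacts after surgery.** Under Surgical procedure: "Wound photographs will be taken on days 3 and 7 by the resident in charge", and later "For post-discharge follow-up at day 30, well-trained investigators blinded to treatment allocation will examine any patient in an outpatient setting".

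The text does not say which of these contacts is a follow-up visit. It also gives no rule for FAS patients whose day-30 SSI status is unknown.

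**The concern.** Intention-to-treat has two parts: every randomised patient is included, and each is analysed in the assigned group. The FAS rule drops the first part, because reaching a follow-up visit happens after randomisation.

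For most endpoints a small exclusion of this kind is a matter of degree. For death it is not, because death before the visit is itself the reason for exclusion. The analysis set then depends on the outcome that it is meant to measure. Reported 30-day mortality would be too low, and on one reading of the text it would be close to zero whatever happened to the patients.

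**Working it through.** **1. The plan's own figures.** The inputs are SSI rates of 12% and 4%, a two-sided chi-square test at 5%, 80% power, 1:1 allocation and 5% drop-out (Statistics/sample size calculation; Randomization and intervention). The article simulates power. I summed the exact binomial probabilities of all outcomes that the uncorrected chi-square test rejects.

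- 170 per arm: power 0.798.
- 172 per arm (344 in total): power 0.8035. The stated 344 is reproduced.
- Drop-out: 344 / 0.95 = 362.1, so 363, made even as 364. This is also reproduced.

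The inflation treats drop-outs as leaving the evaluable number.

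**2. Who leaves the mortality analysis.** The steps follow from the text:

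- Randomisation takes place in the operating room, so any later death is the death of a randomised patient.
- FAS membership needs data from a visit. A patient who dies before the first qualifying visit has none.
- Death within 30 days is analysed on the FAS, so that death is not counted.
- The PPS is drawn from the FAS, so the patient is missing there too.

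The number lost depends on what a follow-up visit is. In the statistics section the term is used for the 30-day visit and the one-year visit. The day-3 and day-7 contacts are described as wound photographs.

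**3. Size.** The article gives neither a mortality rate nor the timing of deaths, so both are assumptions. Let m be true 30-day mortality and s the share of deaths before the first qualifying visit. Suppose nobody else is excluded.

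- Expected deaths = 364 × m
- Deaths removed = 364 × m × s
- Reported rate = m(1 − s) / (1 − m·s)

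Example with m = 0.02 and s = 0.5: 364 × 0.02 = 7.28 deaths, of which 3.64 are removed. The reported rate is 0.010 / 0.990 = 1.01%.

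| m (assumed) | Deaths in 364 | s = 0.10 | s = 0.25 | s = 0.50 | s = 1 |
|---|---|---|---|---|---|
| 1% | 3.6 | 0.4 lost, 0.90% | 0.9 lost, 0.75% | 1.8 lost, 0.50% | all lost, 0% |
| 2% | 7.3 | 0.7 lost, 1.80% | 1.8 lost, 1.51% | 3.6 lost, 1.01% | all lost, 0% |
| 4% | 14.6 | 1.5 lost, 3.61% | 3.6 lost, 3.03% | 7.3 lost, 2.04% | all lost, 0% |

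The last column approximates the reading in which only the day-30 visit qualifies.

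**4. SSI, where the text has no rule.** Suppose, for illustration only, that 5% per arm were lost, were scored as SSI-free, and had all their SSIs missed.

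- Rates: 0.95 × 12% = 11.4% and 0.95 × 4% = 3.8%, a difference of 7.6 points instead of 8.0.
- Power with 182 per arm: 0.803.
- Power if the same patients are excluded (173 per arm): 0.806.

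Balanced loss therefore matters little. Unbalanced loss matters more. With an assumed 10% loss in one arm and none in the other, power is 0.716 if the loss is in control and 0.872 if it is in treatment. With both true rates at 12%, 10% loss in the treatment arm alone gives a rejection rate of 0.065 instead of the nominal 0.05.

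**The case against.** **A full analysis set that needs some post-randomisation data is a common convention.** That is so, and for the wound endpoints the departure from strict intention-to-treat may be slight. It does not help for death, where the missing visit is caused by the event.

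**Asking for at least one visit suggests several qualifying contacts, and inpatients are seen regularly by the study team.** This is a fair reading, and Fig. 1, which was not in the text available to me, may settle it. A reader might infer that the mortality endpoint is empty by construction. That follows only if day 30 is the sole qualifying visit, which the text does not say. Under the wider reading the loss is confined to deaths before the first contact, probably few in elective surgery. It is still not zero by rule.

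**A sensible analyst would accept a recorded death as follow-up data.** Perhaps, but the rule asks for visit data.

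**Patients, surgeons and day-30 assessors are blinded, so loss related to arm is less likely.** This stands. The main effect is understated mortality in both arms and lost events, rather than a demonstrated bias between arms.

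**A reader might also infer that patients lost before day 30 are counted as SSI-free, so that SSI rates are biased downward.** The document does not support this. It states no such rule, and the step from 344 to 364 points the other way. Missing-outcome handling may also sit in an analysis plan that is not shown. What remains is a request to state the rule.

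**Conclusion.** Wrong as written: the analysis set for mortality conflicts with the stated intention-to-treat principle. Patients who die after randomisation and before a qualifying visit are removed from 30-day all-cause mortality, and the PPS repeat cannot bring them back.

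The size is uncertain. For assumed mortality of 1% to 4%, with 10% to 50% of deaths before the first visit, 0.4 to 7.3 deaths are lost. If only the day-30 visit counts, practically all deaths before it are lost. These figures rest on assumed mortality and timing. The exclusion itself rests only on the wording.

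For SSI there is no demonstrated error. The gap is that the only stated robustness check conditions further on complete data, so it cannot show how much missing outcomes matter. No sample-size figure is affected.

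**What to change.** - Define the FAS as all randomised patients, analysed in the group to which they were randomised.
- Analyse 30-day death and length of stay in all of them.
- Define follow-up visit, and say whether the day-3 and day-7 checks count.
- For SSI, state that a patient without day-30 status and without an earlier SSI is not scored as a non-event. Say how patients who die SSI-free before day 30 are handled.
- Add a missing-data sensitivity analysis for SSI on all randomised patients, letting missing outcomes vary in both arms. The choice of method can be left to the analysis plan.
- Keep the PPS repeat, but do not present it as a check on missing data.

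The cost is wording and a few extra analysis runs. Death and length of stay are already planned endpoints, and baseline risk factors are already recorded. The article places all analyses after the last 30-day visit, so the definition can be changed before the arms are compared.

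### The per-protocol set requires complete data on every endpoint, so one missing endpoint removes a patient from all per-protocol analyses, including those where the outcome is known

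*Protocol article*

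**What the plan says.** All of the following is in the Protocol article, mostly in *Statistics/sample size calculation*.

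- The FAS contains "all study participants who were randomized and for whom data from at least one follow-up visit are available".
- The PPS is the part of the FAS "for whom the intervention was completed as planned and for whom complete data on all endpoints" are available. No time window or list of endpoints limits this condition.
- The FAS is the main set. "In addition, all analyses will be repeated using the PPS instead to assess the robustness of the findings".
- The analyses are run "after the last 30-day follow-up visit has taken place".
- *Secondary outcome measures* lists infection within one year after a foreign body is implanted. *Primary outcome measure* also attaches a one-year window for these patients.
- For the one-year data: "Once these data are collected, a final secondary analysis will be done for this subgroup of patients".
- Death within 30 days is a yes/no secondary endpoint, analysed by logistic regression. It is among the analyses to be repeated on the PPS.

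**The concern.** A per-protocol set is meant to show whether the result holds among patients treated as planned. This definition adds a second condition, completeness on every endpoint, which has nothing to do with use of the assigned suture. Three things follow.

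- **All-or-nothing exclusion.** A patient who misses the day-30 visit is lost from the PPS analysis of length of stay, although length of stay is known.
- **Implant patients.** One-year infection is a listed endpoint, but the main analyses come soon after the last 30-day visit. On a literal reading, recently operated implant patients are outside the PPS at that point and could enter it later. Membership then depends on the analysis date.
- **Deaths before day 30.** The article does not say whether their wound data count as complete. If they do not, the set used to repeat the death analysis contains no deaths.

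A difference between the PPS and FAS results could then reflect adherence, missing data or survival, and the reader could not tell which.

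**Working it through.** **1. The plan's own sample size, as a baseline.** Inputs from *Statistics/sample size calculation*: 12% versus 4%, two-sided chi-square test, α = 0.05, power 80%, 5% drop-out. Exact binomial power of the uncorrected chi-square test is 79.8% at 170 per arm, 80.1% at 171 and 80.3% at 172. The stated total of 344 (172 per arm) agrees with this within simulation error: √(0.8 × 0.2 / 10,000) = 0.4 percentage points. Drop-out: 344 / 0.95 = 362.1, so 363, made even at 364. The sample size is not in dispute.

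**2. Patients short of one year at the main analysis.** Inputs from *Trial status*: 280 patients from 12 February 2016 to 12 April 2019, which is 1,155 days.

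- Constant pace: 280 / 1,155 = 0.2424 per day, and × 365 gives about 88 per year.
- Alternative, assuming the last of the remaining 84 patients enrols on 31 December 2019 and the analysis follows 30 days later: the one-year cut-off is 30 January 2019, 72 days before 12 April 2019. Then 72 × 0.2424 + 84 = about 101, or 28% of 364.

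Only the implant patients among these are affected. The article gives no implant share, so the shares below are assumptions.

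| Assumed implant share | Lost, of 88 | Lost, of 101 |
|---|---|---|
| 5% | 4 | 5 |
| 10% | 9 | 10 |
| 20% | 18 | 20 |
| 50% | 44 | 51 |

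The 9 to 18 patients at shares of 10 to 20% are 9 / 364 = 2.5% to 18 / 364 = 4.9% of the trial. The whole table spans about 1% to 14%.

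**3. Cost in precision.** Patients per arm = 182 × 0.95 × (1 − fraction lost), rounded down. Power is exact, at 12% versus 4%.

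| Fraction of all patients lost | Per arm | Power |
|---|---|---|
| 0 | 172 | 80.3% |
| 2.5% | 168 | 79.3% |
| 5% | 164 | 78.2% |
| 10% | 155 | 75.5% |
| 20% | 138 | 71.2% |

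A loss of 9 to 18 patients costs about 1 to 2 points of power in a sensitivity analysis. Under *Surgical procedure*, the envelope is opened immediately before wound closure. Implantation and operation date are therefore presumably fixed before allocation, and dropping these patients should not by itself bias the comparison of arms.

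**4. Deaths, if counted as incomplete.** The PPS death analysis then has 0 events in both arms, and the odds ratio is not estimable. For infection, the comparison is among survivors. With mortality a after infection and b without, taken as equal in both arms, the rate among survivors is p(1 − a) / [p(1 − a) + (1 − p)(1 − b)]. The values of a and b are assumptions.

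- a = 10%, b = 1%: control 0.108 / 0.9792 = 11.0%; treated 0.036 / 0.9864 = 3.6%; difference 7.4 points instead of 8.0.
- a = 20%, b = 1%: control 0.096 / 0.9672 = 9.9%; treated 0.032 / 0.9824 = 3.3%; difference 6.7 points.

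**The case against.** The strongest case on the other side has four parts.

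- **Deaths.** A reader might infer that the definition removes every patient who dies, so that the PPS death analysis is empty by construction. The article does not say so. Death is itself an endpoint and is fully observed in a patient who dies. The wound endpoints are events within 30 days, and *Surgical procedure* provides for ward registration, consultant verification and regular inpatient review. Events before an in-hospital death can therefore be recorded. This stands: exclusion of deaths is conditional on a rule the text does not give.
- **One-year data.** The article defers these to a later subgroup analysis, so endpoints at the main analysis may have been meant as the 30-day ones. That is a reasonable reading. It does not remove the problem, because the definition says all endpoints and one-year infection is listed among them.
- **Robustness.** A reader might infer that the PPS cannot test robustness at all, or that it selects patients with an uncomplicated course. Neither is supported. Patients with infection, dehiscence or re-operation stay in if their data are complete. The loss of recent implant patients mainly costs precision, and the FAS remains the main set.
- **Detail for the analysis plan.** A separate analysis plan may exist, and such detail is often left to it. But here the article does not leave a gap. It states a rule, and the rule is badly fixed.

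**Conclusion.** The point holds in limited form. The completeness condition ties PPS membership to endpoints that a given analysis does not use. Applied literally, it drops patients whose 30-day infection outcome is known, for reasons unrelated to the assigned suture.

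For implant patients the size is about 9 to 18, assuming a 10 to 20% implant share and a constant enrolment pace of about 88 a year. The effect is mainly on precision, assuming implantation precedes allocation.

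For deaths the consequence depends on coding that the article leaves open. If they count as incomplete, the PPS analysis of 30-day death cannot be carried out, and the infection contrast is conditioned on survival (7.4 to 6.7 points instead of 8.0 under the assumed mortality).

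The completeness condition does not touch the FAS analysis, so the main conclusion of the trial is not at risk. The definition should be corrected so that the PPS repeat can be interpreted.

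**What to change.** Before unblinding, replace the PPS definition with one based on adherence: randomised, eligible, assigned suture used as planned, no major deviation. Require data only for the endpoint and time window of the analysis in question, so that the 30-day analyses do not depend on one-year data. State that patients who die before day 30 stay in the PPS for the 30-day death analysis, and state how their wound endpoints are coded.

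This takes two or three sentences and no new data. The downside is that the number analysed may differ slightly between PPS endpoints, so each should be reported with its own denominator. Limiting the PPS repeat to the primary endpoint would also be possible, but that is a preference and is not needed to cure the defect.
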